**Objective:**

Primary objective is to assess the association between VET clotting time (CT) in Russell viper venom (RVV) assay and Anti-Xa activity. Secondary objectives include assessing whether VET or Anti-Xa aligns more closely with global haemostatic function, defined by thrombin generation assay (TGA) variables. Exploratory analyses aim to characterise associations among VET parameters, standard laboratory tests, and biomarkers; model dose–exposure–response relationships; and identify clinical modifiers as sepsis or renal dysfunction. Sepsis status will be incorporated as predefined effect modifier in mixed-effects models.

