#### Primary analysis

2.13.1

The primary outcome, defined as the correlation between Anti-Xa activity (UFH/LMWH) and CT in the RVV-assay. Because two measurements per patient are planned, the primary inferential analysis will be conducted using a linear mixed-effects model including:

A random intercept for patientA fixed effect for anticoagulant type (UFH vs. LMWH)

This approach accounts for intra-individual correlation and avoids inflation of type I error due to non-independence of repeated observations. Results will be reported as regression slope estimates (per 0.1 IU/mL increase in Anti-Xa activity) with 95% confidence intervals. For descriptive comparability with previous literature, Spearman rank correlation coefficients with bootstrap-derived 95% confidence intervals will additionally be reported:

For the overall cohortStratified by anticoagulant type

Passing–Bablok regression will be applied as a robust method-comparison technique to assess proportional and systematic bias between CT-RVV and Anti-Xa activity (36). Proportional bias will be considered absent if the 95% confidence interval (CI) of the slope includes 1.0, and constant bias absent if the 95% CI of the intercept includes 0.

These criteria are used for methodological characterization rather than to demonstrate assay equivalence. The primary objective is not interchangeability but to determine whether CT-RVV exhibits a stable monotonic relationship with Anti-Xa activity under ICU conditions.

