### Handling for repeated measurements

2.14

All inferential analyses involving repeated measurements will apply mixed-effects modelling with patient-level random intercepts. Simple correlation coefficients are presented for descriptive purposes only.

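### The Passing–Bablok bias criteria (slope 1.0, intercept 0) have no meaning when a clotting time is regressed on an activity in IU/mL, and should be dropped

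*Protocol article*

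**What the plan says.** Section 2.13.1 (Primary analysis) sets out three analyses of CT-RVV and Anti-Xa. The primary inference is a linear mixed-effects model: "Results will be reported as regression slope estimates (per 0.1 IU/mL increase in Anti-Xa activity) with 95% confidence intervals". Spearman coefficients follow as description. The third is the one at issue: "Passing–Bablok regression will be applied as a robust method-comparison technique to assess proportional and systematic bias between CT-RVV and Anti-Xa activity".

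Its decision rule has two parts. The slope is judged first: "Proportional bias will be considered absent if the 95% confidence interval (CI) of the slope includes 1.0". A companion rule, which judges the other fitted coefficient in the same way, declares "constant bias absent if the 95% CI of the intercept includes 0". A caveat follows: "These criteria are used for methodological characterization rather than to demonstrate assay equivalence". The section adds that the aim is a stable monotonic relationship and not interchangeability.

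The abstract defines the VET variable as "VET clotting time (CT) in Russell viper venom (RVV) assay", so it is a time. Its unit is not printed. No section calibrates, converts or standardises CT to the Anti-Xa scale before the comparison.

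**The concern.** Passing–Bablok with slope 1 and intercept 0 as the no-bias reference answers one question: do two methods that report the same quantity in the same unit agree? Between a time and an activity, the slope is in time per IU/mL and the intercept is a time. The values 1.0 and 0 then have no special standing, and proportional and constant bias are undefined. The same section treats the mixed-model slope correctly as a quantity with units, then holds the Passing–Bablok slope to a unit-free 1.0.

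At stake is a pre-specified bias verdict, under the primary-analysis heading, in a study that asks whether VET can stand in for Anti-Xa. As written, that verdict carries no usable information about the assay, and its intercept half can point the wrong way.

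**Working it through.** The plan gives no figure to reproduce, because the rule consists of fixed reference values. The check is how the verdict behaves.

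**Inputs from the article.** Slope reference 1.0 and intercept reference 0 (2.13.1); Anti-Xa in IU/mL (2.13.1); total n = 66 and planning correlations of 0.669 (LMWH) and 0.6 (UFH) (2.12).

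**Assumptions, not in the article.** CT in seconds. Anti-Xa mean 0.35, SD 0.15 IU/mL. Scenario A: CT mean 120, SD 40 s. Scenario B: heparin-free CT 70 s, rising 100 s per IU/mL. Simulations use 66 independent pairs.

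**Step 1, units.** Write CT = a + b × AntiXa. If CT is multiplied by f and Anti-Xa by g, the slope becomes b × f/g and the intercept a × f. Any positive slope can be turned into 1.0 by choosing g = b × f.

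**Step 2, plausible size of the slope.** The Passing–Bablok slope is roughly SD(CT)/SD(Anti-Xa). For CT SDs of 10 to 80 s and Anti-Xa SDs of 0.1 to 0.4 IU/mL:
- In seconds: 10/0.4 = 25 to 80/0.1 = 800 s per IU/mL, never near 1.
- In minutes: 25/60 = 0.4 to 800/60 = 13.3 min per IU/mL, a range that contains 1 by accident of unit.

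**Step 3, one near-perfect data set (scenario A, correlation 0.999), with only the units changed.**

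| Units | Slope (95% CI) | Verdict under the rule |
|---|---|---|
| s vs IU/mL | 267.3 (264.2 to 270.5) | bias |
| min vs IU/mL | 4.45 (4.40 to 4.51) | bias |
| s vs 0.1 IU/mL | 26.7 (26.4 to 27.1) | bias |
| s vs IU/L | 0.267 (0.264 to 0.270) | bias |
| s vs units of 0.00375 IU/mL | 1.00 (0.99 to 1.01) | no bias |

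The last unit is simply 0.15/40 = 0.00375, which equalises the two SDs.

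**Step 4, 500 repeats of scenario A.** The slope interval included 1.0 in 0% of runs in s or min per IU/mL, and in 94.6% with the rescaled unit. Both figures were the same at correlations 0.6 and 0.95, so the slope verdict did not respond to assay quality.

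**Step 5, the intercept in scenario B, in seconds.** Residual SD = 100 × 0.15 × √(1/r² − 1), which is 20.0 s at r = 0.6, 16.7 s at 0.669 and 4.9 s at 0.95. The interval included 0 in about 94% of runs at r = 0.6 (91% in a second set of runs), 60% at r = 0.669 and 0% at r = 0.95. The slope interval never included 1.0, also at r = 0.99. The noisy assay usually passes as free of constant bias, and the precise one always fails.

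The mechanism is that noise inflates the fitted slope. At r = 0.65 with 100 pairs and the scenario B line, mean fitted slopes were 224 to 328 against a true 100, across four assumed Anti-Xa distributions. Mean fitted intercepts were then about −2 to 22 s against a true 70.

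**Step 6, the intercept also moves with units.** In scenario A at correlation 0.6, the interval included 0 in 60% of runs (s vs IU/mL), 90% (min vs IU/mL) and 2% (s vs IU/L). The classical estimator shifts its median by the number of pairwise slopes below −1, so it does not simply rescale. In one data set at correlation 0.6 the slope was 535.2 in seconds; dividing by 60 gives 8.92, but the fit in minutes gave 7.45.

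**The case against.** The strongest defence is that the analysis is peripheral and already hedged. The primary inference is the mixed model. The outcome list in section 2.10 names Spearman correlation and mixed-effects regression and does not mention Passing–Bablok. Sample size, effect modification and analysis population do not depend on it. Section 2.13.1 disclaims equivalence, and section 2.1 calls the study primarily hypothesis-generating. All of this stands and limits the consequence. It does not make the rule valid: agreement is the only question these criteria answer, the plan says that is not its question, and the rule still returns a verdict.

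Four stronger readings are tempting and are not supported.
- A reader might infer that constant bias will be declared however well CT tracks Anti-Xa, or that only a change of unit could reverse it. Step 5 shows otherwise: at the planning correlations the intercept interval often includes 0 with no change of unit.
- A reader might equate the fitted intercept with the heparin-free clotting time. That holds only when the correlation is high.
- A reader might infer that the primary result is compromised. It is not.
- A reader might see a contradiction with section 2.14: "All inferential analyses involving repeated measurements will apply mixed-effects modelling with patient-level random intercepts". Passing–Bablok as described makes no allowance for two samples per patient, and a rule based on confidence intervals looks inferential. But section 2.13.1 labels it characterization, so this is a fair question and not a clear contradiction.

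**Conclusion.** The concern holds for the decision rule: it is wrong as written and should be fixed. That the criteria are undefined across units follows from the article alone and needs no simulation; any unit of time gives the same conclusion.

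The sizes rest on the assumed distributions. The slope verdict is set by units: 0% of intervals included 1.0 in seconds or minutes per IU/mL in both scenarios, against 94.6% in scenario A after an arbitrary rescaling. In minutes, other assumed SDs could bring the slope near 1 by accident, which illustrates the same fault. The intercept verdict depends on noise and units and can reward the worse assay (about 94%, 60% and 0% at r = 0.6, 0.669 and 0.95 in scenario B). The harm is a misleading auxiliary result, with no loss of the primary estimate.

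**What to change.** In section 2.13.1, and in the analysis plan that section 2.13 says is finalised before database lock, delete the Passing–Bablok regression of CT-RVV on Anti-Xa together with the slope 1.0 and intercept 0 criteria. Rely on the mixed-model slope and the Spearman coefficients, which already address the stated aim.

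Optionally, if a method comparison is still wanted, first convert CT to a predicted Anti-Xa in IU/mL, cross-validated by patient. Then report bias and limits of agreement against measured Anti-Xa with a repeated-measures variance. That would examine interchangeability, which the plan says is not its objective, so it is not needed to correct the error.

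The deletion costs a wording change and removes one analysis. The option needs some extra code. Neither needs new data.

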#### Pre-specified effect modification analyses

2.13.2

To explicitly address biological heterogeneity in critically ill patients, potential effect modifiers will be analysed within the mixed-effects framework using interaction terms.

Pre-specified modifiers include:

Sepsis statusAntithrombin concentrationRenal function (creatinine, estimated GFR)Inflammatory markers (CRP, fibrinogen, albumin)

Sepsis status will be analysed as an effect modifier rather than as a separately powered subgroup.

These analyses aim to identify conditions under which CT-RVV and Anti-Xa activity diverge.

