### Sample size

2.12

This study is designed to evaluate the association between Anti-Xa activity and VET variables, with a primary focus on CT in the RVV test, in critically ill patients receiving LMWH or UFH. The planned sample size allows estimation of this association under real-world ICU conditions and supports pre-specified mixed-effects modelling incorporating a limited number of biologically plausible effect modifiers. To account for heterogeneity in coagulation physiology, anticoagulant type (LMWH vs. UFH) and sepsis status will be examined as predefined effect modifiers within the modelling framework. These factors will not be treated as independently powered subgroups but will be analysed using interaction terms. The study is not powered for definitive detection of small correlation coefficients nor for confirmatory subgroup comparisons. Stratified analyses are therefore considered exploratory and hypothesis-generating. Findings will be interpreted cautiously and are intended to inform the design of future adequately powered multicentre studies.

The study is powered for estimation of the Anti-Xa–CT association. Analyses involving thrombin generation are predefined as secondary and exploratory. No separate formal sample size calculation was performed for TGA-CT correlations, as these analyses are hypothesis-generating. The sample size estimation was based on published data reporting a significant Spearman correlation for LMWH-treated patients between Anti-Xa levels and CT-RVV (*r* = 0.669, *p* = 0.0395) (34). For UFH, no exact coefficient was reported, although the same study demonstrated a clear association. For conservative planning, an effect size of *r* = 0.6 was assumed for UFH.

Calculations were performed with G*Power 3.1 (35) for a two-sided test of correlation (*α* = 0.05, power = 0.80). The required sample sizes were 19 independent observation pairs for *r* = 0.669 and 23 pairs for *r* = 0.6. As two temporally separated measurements are planned per patient, the non-independence of repeated measures was adjusted using a design effect with an intraclass correlation coefficient (ICC) of 0.3:

Design−Effect=1+(2−1)×0.3=1.3

$$\text{Effective observations}\;\mathrm{per}\;\text{patient}=\frac{2}{1.3}\approx 1.54$$

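### Section 2.12 predefines anticoagulant type as an effect modifier, but 2.13.1 and 2.13.2 do not carry this through, and nothing keeps drug × Anti-Xa in the models that test sepsis, renal function and the other modifiers

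*Protocol article*

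**What the plan says.** Three sections of the protocol article bear on this.

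- **2.12 Sample size:** "anticoagulant type (LMWH vs. UFH) and sepsis status will be examined as predefined effect modifiers within the modelling framework". The next sentence adds: "These factors will not be treated as independently powered subgroups but will be analysed using interaction terms".
- **2.13.1 Primary analysis:** the linear mixed model has a random intercept for patient and a "fixed effect for anticoagulant type (UFH vs. LMWH". No product of drug and Anti-Xa is listed. On output: "Results will be reported as regression slope estimates (per 0.1 IU/mL increase in Anti-Xa activity) with 95% confidence intervals". Spearman coefficients are also given by drug, for description only.
- **2.13.2 Pre-specified effect modification analyses:** "potential effect modifiers will be analysed within the mixed-effects framework using interaction terms". The modifiers named are sepsis status, antithrombin, renal function (creatinine, eGFR) and inflammatory markers (CRP, fibrinogen, albumin). Anticoagulant type is not among them. The stated purpose is: "These analyses aim to identify conditions under which CT-RVV and Anti-Xa activity diverge".

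The other lists of modifiers, in 2.10 (exploratory outcome 4) and 2.16, do not name anticoagulant type either.

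**The concern.** The slope of CT-RVV on Anti-Xa may differ between UFH and LMWH, and 2.12 treats that as credible by naming drug as a modifier. The study is observational with consecutive enrolment, so nothing balances drug across sepsis, renal function, antithrombin or inflammation. When both conditions hold, a model with Anti-Xa, drug, the modifier and modifier × Anti-Xa, but without drug × Anti-Xa, is misspecified. The modifier interaction then picks up part of the drug difference.

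A drug main effect does not prevent this, because it shifts the intercept and leaves the slope common to both drugs. Testing drug as a modifier in a model of its own does not prevent it either, because the sepsis or renal model still lacks the term.

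These analyses are meant to say in which patients the two assays part company, and the Introduction makes defining those conditions part of the primary objective. Without the term they could point to sepsis or renal dysfunction when heparin type is the cause. They could also hide a real modifier if the two effects run in opposite directions.

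**Working it through.** The plan gives no figure for this point, so there is none to reproduce. The check is on the mechanism and its size.

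**Inputs from the protocol (2.12).** 30 LMWH and 36 UFH patients, two measurements each; ICC 0.3; planning correlations r = 0.669 (LMWH) and r = 0.6 (UFH); α = 0.05 two-sided.

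**Assumptions, not in the protocol.** Drug-specific slopes, and the share of septic patients under each drug.

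**Step 1: correlations read as slopes.** With Anti-Xa and residual both at SD 1, slope = r/√(1 − r²).
- LMWH: 0.669/√(1 − 0.669²) = 0.90
- UFH: 0.6/√(1 − 0.6²) = 0.75

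This is only one possible reading. A correlation does not fix a slope, because residual SDs can differ.

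**Step 2: expected bias.** With no true sepsis effect, the spurious sepsis × Anti-Xa coefficient is roughly (UFH slope − LMWH slope) × (septic share in UFH − septic share in LMWH). At 70% vs 30%:
- UFH slope 0.75: (0.75 − 0.90) × 0.40 = −0.06
- 0.45: −0.45 × 0.40 = −0.18
- 1.35: 0.45 × 0.40 = +0.18
- 1.80: 0.90 × 0.40 = +0.36

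**Step 3: simulation.** 2,000 runs per setting, no true sepsis effect on the slope, same Anti-Xa distribution in both drugs, common residual SD. Generalised least squares with the random-intercept correlation set at 0.3 was fitted without and with drug × Anti-Xa. Mean spurious coefficients at 70/30 without the term were −0.06, −0.18, +0.19 and +0.36, matching step 2. With the term they were about 0.

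Rejection rate (%) for the null sepsis × Anti-Xa term, LMWH slope 0.90, by septic share in UFH/LMWH:

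| UFH slope (ratio) | 50/50 | 60/40 | 70/30 | 80/20 | with drug × Anti-Xa, all splits |
|---|---|---|---|---|---|
| 0.75 (0.83) | 5.6 | 6.5 | 6.2 | 8.5 | 4.7 to 6.6 |
| 0.45 (0.5) | 6.2 | 8.5 | 17.2 | 32.7 | 4.3 to 5.3 |
| 1.35 (1.5) | 7.3 | 8.9 | 19.5 | 33.7 | 4.3 to 6.2 |
| 1.80 (2) | 10.2 | 21.3 | 45.8 | 78.2 | 4.9 to 5.5 |
| 2.70 (3) | 20.8 | 39.5 | 79.8 | 97.0 | 4.2 to 5.1 |

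Monte Carlo error near 5% is √(0.05 × 0.95/2000), about 0.5 percentage points. In the 50/50 column the mean bias is about zero. Rejection still exceeds 5% when slopes differ widely; sepsis was drawn at random per patient, so single samples are imbalanced by chance.

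**Step 4: a second set-up.** 800 runs, REML fits, Anti-Xa ICC 0.5, residual ICC 0.3, and residual SD set separately for each drug so that r stays at 0.669 and 0.6. A steeper UFH slope then brings more UFH noise. Modifier prevalence in UFH/LMWH was 50/30, 60/25 and 70/15.
- Ratio 1.5: 7%, 11%, 16%
- Ratio 2: 11%, 15%, 30%
- Ratio 3: 16%, 25%, 49%
- With drug × Anti-Xa: 6% to 8%, bias about 0
- Equal slopes: about 6% with or without the term

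The pattern is the same and the rates are lower.

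**Step 5: price of the term.** In step 3 with UFH slope 0.75, the standard error of the sepsis interaction goes from 0.180 to 0.186 at 60/40 (0.186/0.180 = 1.03), to 0.202 at 70/30 (1.12) and to 0.237 at 80/20 (1.32). In step 4 with equal slopes the rise is about 4% to 28%.

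**The case against.** The strongest reply is that the protocol does provide for a drug interaction. Section 2.12 commits to it, 2.13.2 introduces its list as one that includes the named items without calling it complete, and nothing says modifiers are tested one at a time or that drug × Anti-Xa is left out of the sepsis model. This stands against a reading that a reader might take from 2.13 alone, namely that the plan contains no drug-by-Anti-Xa term at all. It does not settle the point: 2.12 promises that drug will be examined as a modifier, not that its interaction stays in the models for other modifiers, and only the latter removes the bias.

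A second reply is that which terms share a model is normally left to the analysis plan, which 2.13 mentions and which is not shown. That is fair for the detail, and that plan may already specify it. It does not cover the disagreement inside the article, where 2.12 calls drug an effect modifier, 2.13.1 gives it a main effect and 2.13.2 leaves it out.

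Third, the size rests on assumed slopes and prevalences. This stands in full. Under the only drug-specific planning figures, read as slopes, the inflation is small.

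Fourth, the protocol calls the study primarily hypothesis-generating and its stratified analyses exploratory, and it reports Spearman coefficients by drug. The exploratory label deals with power and strength of claim, but not with bias. Drug-specific correlations could show a marked difference in strength of association, but they do not adjust the sepsis or renal interaction for it.

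**Conclusion.** The point holds as an internal inconsistency with a conditional statistical consequence. Sections 2.12, 2.13.1 and 2.13.2 do not agree on the role of anticoagulant type, and no section protects the clinical-modifier results from a drug difference in slope.

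At an assumed 70/30 septic split, the false-positive rate for a null sepsis modifier runs from about 6% (slopes 0.90 and 0.75) through about 20% (ratio 1.5) to about 46% (ratio 2), and returns to about 5% with the term. Holding the planned correlations fixed gives lower rates, for example 30% at ratio 2 with a 70/15 split.

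A reader might infer that a reported sepsis or renal effect will be a drug artefact. The protocol does not support that: it gives no drug-specific slopes and no modifier prevalence by drug, and the bias disappears if either the slopes or the prevalences are equal. What can be said is that the plan as published does not rule the artefact out, although doing so is cheap.

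**What to change.** Reconcile 2.12 with 2.13.1 and 2.13.2 by listing anticoagulant type as a modifier in 2.13.2. State there that each clinical-modifier model contains Anti-Xa, drug, the modifier, Anti-Xa × drug and Anti-Xa × modifier, and that modifier conclusions, still exploratory, are read from that model. Adding the drug interaction to the primary model alone would not be enough.

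The cost is a sentence or two, one degree of freedom per model and some precision. The loss is small when drug and modifier overlap little and reaches roughly 30% in standard error when they overlap strongly, which is where the protection matters most if the slopes differ. With 66 patients that loss is real and should be accepted openly. A table of each modifier by drug would let readers see the overlap, but it is optional.

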1) Variable: Additional VET variables (CFT, A5, A10, MCF, *α*-angle, lysis time, and lysis index).Metric: Spearman correlations with Anti-Xa and TGA variables; multivariable mixed-effects regression to account for repeated measures.Aggregation: Correlation coefficients (*r*) with 95% CI; regression *β* with 95% CI.Time point: As in primary outcome.Clinical relevance: Explores whether extended VET variables provide complementary or superior information to CT for characterizing anticoagulant effect.2) Variable: Advanced haemostatic biomarkers (PF1 + 2, TAT, PAP, PAI-1, TFPI, FVIII, FXIII).Metric: Correlation with Anti-Xa, VET, and TGA; exploratory path analyses of marker interrelations.Aggregation: Correlation coefficients with 95% CI; descriptive effect-size comparison.Time point: Parallel to VET and TGA sampling.Clinical relevance: Identifies mechanistic markers that may explain discordance between concentration-based assays (Anti-Xa) and functional assays (VET/TGA).3) Variable: Dose-exposure-response relationships (applied dose, Anti-Xa levels, VET, and TGA).Metric: Linear and nonlinear regression models linking administered anticoagulant dose to laboratory readouts.Aggregation: Regression coefficients (*β*) with 95% CI; model fit indices (*R*^2^, AIC).Time point: At all scheduled samplings, stratified by regimen type.Clinical relevance: Assesses whether dosing strategies achieve expected anticoagulant activity defined as Anti-Xa activity within the intended target range regarding dosage and whether functional assays reveal discrepancies not captured by Anti-Xa.4) Variable: Patient-level modifiers (e.g., sepsis status, SOFA score, renal function, albumin, BMI).Metric: Interaction terms in regression/mixed-effects models; subgroup analyses.Aggregation: *β* coefficients for interaction effects with 95% CI; stratified correlation estimates.Time point: As in primary outcome, stratified by clinical subgroup.Clinical relevance: Determines whether specific patient factors systematically influence anticoagulant effect or modify the correlation between Anti-Xa, VET, and TGA.5) Variable: Clinical complications (bleeding and thrombotic events within 24 h).Metric: Exploratory descriptive analysis of concordance between laboratory profiles and event occurrence; logistic regression if case numbers allow.Aggregation: Odds ratios with 95% CI (if feasible); otherwise descriptive frequencies.Time point: Event assessment in the 24 h prior to or following each sampling.Clinical relevance: Provides preliminary signal on the clinical predictive value of Anti-Xa, VET, and TGA in identifying patients at bleeding or thrombotic risk.

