
Sepsis, multi-organ failure, and endothelial dysfunction alter pharmacokinetics and pharmacodynamics, complicating both drug absorption and elimination. Consequently, Anti-Xa monitoring provides only a concentration-based readout and does not reflect the complex interplay between the procoagulant and anticoagulant pathways. In particular, it neglects the influence of elevated fibrinogen levels due to inflammation, increased platelet activation, and impaired fibrinolytic activity. Similarly, standard laboratory tests such as aPTT and INR are confounded by acute-phase reactants and inflammatory mediators. Additionally, Anti-Xa activity reflects heparin-dependent inhibition of a fixed amount of exogenous factor Xa and is therefore largely independent of endogenous factor X levels. In contrast, CT-RVV in whole blood may be influenced by variations in coagulation factor concentrations, including factors V and X. Such variability is considered part of the biological context of critical illness and is not treated as methodological noise but as a potential modifier of assay concordance. As a result, neither Anti-Xa nor conventional coagulation tests adequately capture the dynamic risk of bleeding and thrombosis in critically ill patients.

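### The readouts named for the modifier analyses do not respond to a constant shift in CT-RVV at equal Anti-Xa, so a condition that shifts CT in parallel could be reported as showing no divergence

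*Protocol article*

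**What the plan says.** Section 2.13.2 lists sepsis status, antithrombin, renal function and inflammatory markers (CRP, fibrinogen, albumin). On the tool it says that "potential effect modifiers will be analysed within the mixed-effects framework using interaction terms". On the aim it says: "These analyses aim to identify conditions under which CT-RVV and Anti-Xa activity diverge".

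Exploratory outcome 4 in section 2.10 covers the patient-level modifiers. Its metric is "Interaction terms in regression/mixed-effects models; subgroup analyses", and the results to be reported are "coefficients for interaction effects with 95% CI; stratified correlation estimates".

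The primary analysis in section 2.13.1 is also read through a slope: "Results will be reported as regression slope estimates (per 0.1 IU/mL increase in Anti-Xa activity) with 95% confidence intervals". Its declared purpose is to "determine whether CT-RVV exhibits a stable monotonic relationship with Anti-Xa activity under ICU conditions".

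The Introduction gives the use in view. CT-RVV is to serve as a quick bedside stand-in when Anti-Xa is delayed, and the study should define the conditions under which the relationship worsens. The abstract likewise treats a consistent correlation across clinical states as support for monitoring by VET.

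**The concern.** Reading CT in place of Anti-Xa needs two things to hold across conditions: the slope, and the level of CT at a given Anti-Xa. The named readouts address the slope and the tightness of the relationship within strata. Neither addresses the level.

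Suppose septic patients have the same slope and scatter as the others, but a CT longer by a fixed amount throughout. The interaction coefficient would be near zero and the two stratified correlations would agree. By the article's own reasoning that pattern supports bedside use. Yet a reader applying one CT-to-Anti-Xa relation to both groups would misjudge Anti-Xa in at least one of them, always in the same direction. The study sets out to find conditions of this kind, and the listed outputs could report none.

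**Working it through.** **Plan figures.** The article gives no figure for detecting modifier effects, so there is none to reproduce. From section 2.12 I take 66 patients (36 on UFH), two samples each, ICC 0.3 and r = 0.6. The article assumes r = 0.6 for UFH; using it for the whole cohort is my assumption. Sepsis share and shift size are not in the document and are also assumed.

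**Algebra.** Let X be Anti-Xa and M the modifier (0 or 1):

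CT = b0 + b1·X + b2·M + b3·M·X + anticoagulant type + patient intercept + error

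- The CT difference between modifier levels at X = x is b2 + b3·x.
- A parallel shift of size d means b2 = d and b3 = 0. The interaction readout b3 is therefore zero whatever d is.
- Adding d to every CT in one stratum leaves the ranks within that stratum unchanged, so its Spearman coefficient is exactly unchanged.
- Reading CT back through the unshifted line misjudges Anti-Xa by d / b1.

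These results do not depend on any simulation.

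**Size of the misreading.** With CT and Anti-Xa in SD units and r = 0.6, the slope is 0.6 and the residual SD is √(1 − 0.36) = 0.8. A shift of 1 residual SD gives 0.8 / 0.6 = 1.33 SD of Anti-Xa. A shift of 0.5 gives 0.4 / 0.6 = 0.67 SD.

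**Simulation.** The model above was fitted by generalised least squares at the known ICC, with 50% septic and 4,000 runs per row (Spearman means from 800 runs). Anti-Xa has mean zero, so the level term b2 is the CT difference at average Anti-Xa.

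| Constant shift in sepsis (residual SD) | Interaction rejects | Level term rejects | Spearman non-septic / septic | Pooled Spearman |
|---|---|---|---|---|
| 0 | 5.4% | 4.8% | 0.58 / 0.58 | 0.58 |
| 0.5 | 5.0% | 69% | 0.57 / 0.58 | 0.57 |
| 1 | 4.8% | 99.9% | 0.57 / 0.57 | 0.53 |
| 2 | 4.9% | 100% | 0.58 / 0.57 | 0.44 |

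**Sensitivity.**
- 40% septic: interaction about 5%; level term 68% (0.5 SD) and 99.9% (1 SD).
- 30% septic, 1 SD shift: 4.2% and 99%.
- r = 0.3 with 40% septic: interaction 4.3 to 4.6%; level term 65% and 99.9%.
- A full mixed-model fit without the anticoagulant term (200 runs, 1 SD shift): 4% and 100%.
- Converse case, slope halved in sepsis with no shift at average Anti-Xa: interaction 55%, level term 5%.

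The last line shows that neither term replaces the other. The pooled correlation gives little warning: a 1 SD shift moves it only from 0.58 to 0.53.

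**Other sections.** The constant-bias criterion of the Passing–Bablok analysis in 2.13.1 is not applied by modifier. Section 2.16 again relies on interaction terms. Section 2.13.3 plans multivariable mixed models with standardised coefficients for a laboratory family that includes antithrombin, fibrinogen and albumin. It names no response variable and no divergence aim, and the family leaves out sepsis, creatinine or eGFR, and CRP.

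**The case against.** The strongest reply is that the gap is a missing reading rule and not a blind model. A standard interaction model contains the modifier's own term, and nothing in the article removes it, so a parallel shift would normally be estimated. This stands. A reader might infer that the plan would certainly pass a shifted condition as stable; the article supports only that it could.

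A reader might also infer that interaction terms are the only route by which a modifier can show an effect. That goes too far. Outcome 4 lists subgroup analyses, its stated purpose includes whether patient factors systematically influence the anticoagulant effect, and 2.13.3 covers three of the listed modifiers. The gap is clearest for sepsis, renal function and CRP.

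A third tempting inference is that the authors themselves predict a constant shift, because the Discussion says that "CT-RVV in whole blood may be influenced by variations in coagulation factor concentrations, including factors V and X". That sentence makes a level effect plausible, but it does not say that the effect is equal at all Anti-Xa levels. Factors V and X are neither listed modifiers nor collected variables.

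It is also fair to say that the simulated shift is built in, that an interaction test rejecting at its nominal 5% is no surprise, that these analyses are exploratory, and that the article disclaims interchangeability of the assays. All of this limits the weight of the point.

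The analysis plan is not shown and may define the contrasts. However, the article itself names the aim, the tool and the reported quantities, and the quantities do not fit the aim. That is a mismatch in what is written, not a detail left out.

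**Conclusion.** The point holds in limited form. The readouts named for the modifier analyses cannot register a parallel shift in CT-RVV, and no section makes such a shift count as divergence. A condition that changes what a given CT means could therefore be reported as showing none.

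The blindness of the two readouts is exact. Its practical size is not known from the document. The 5% against 68 to 69% and 99.9%, and the misreading of 0.67 to 1.33 SD of Anti-Xa, illustrate shifts of 0.5 and 1 residual SD at r = 0.6 and are not predictions for this study.

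The change is worth making because finding where the relationship worsens belongs to the primary objective as the Introduction states it. No confirmatory conclusion is at risk.

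**What to change.** In section 2.13.2 and exploratory outcome 4, add a second divergence measure beside the interaction coefficient: the model-based difference in expected CT-RVV between modifier levels at two or three fixed Anti-Xa values within the observed range, with 95% CI, from the same mixed model. For continuous modifiers, name the two values to be compared. State that a difference in level counts as divergence as well as a difference in slope. Fixed Anti-Xa values are better than the bare level term, which in an uncentred model refers to Anti-Xa of zero.

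Optionally, also give the difference in Anti-Xa equivalents (difference divided by slope). A joint test of level and interaction on two degrees of freedom is optional too; it is slightly less sensitive to a pure slope change, and the plan should say so.

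The cost is a few sentences in the protocol and analysis plan. The model, samples and patients stay as planned.
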